## Abstract

**Background:**

The World Health Organization initiated test, treat, and track (T3) malaria strategy to support malaria-endemic countries in their efforts to achieve universal coverage with diagnostic testing, antimalarial treatment, and strengthening surveillance systems. Unfortunately, T3 is not adopted by over-the-counter medicine sellers (OTCMS) where many patients with malaria-like symptoms first seek treatment. Sub-Saharan African countries are considering introducing and scaling up RDTs in these outlets to reduce malaria burden. In this context, this study is aimed at improving implementation of the T3 among OTCMS using a number of intervention tools that could be scaled-up easily at the national level.

**Methods/design:**

The interventions will be evaluated using a two-arm, cluster randomized trial across 8 rural communities (4 clusters per arm), in two adjacent districts (Fanteakwa North and Fanteakwa South districts) of Ghana. A total of 8 OTCMS in the intervention arm and 5 OTCMS in the control arm in the selected communities will participate in the study. In the intervention arm only, subsidized malaria rapid diagnostic test (mRDT) kits will be introduced after the OTCMS have been trained on how to use the kit appropriately. Supervision, technical assistance, feedbacks, and collection of data will be provided on a regular basis at the participating medicine stores. The primary outcome is the proportion of children under 10 years with fever or suspected to have malaria visiting OTCMS and tested (using mRDT) before treatment. Secondary outcomes will include adherence to national malaria treatment guidelines and recommended mRDT retail price. Outcomes will be measured using mainly a household survey supplemented by mystery client survey and a surveillance register on malaria tests conducted by the OTCMS during patient consultations. Data collected will be double entered and verified using Microsoft Access 2010 (Microsoft Inc., Redmond, Washington) and analyzed using STATA version 11.0.

**Discussion:**

The trial will provide evidence on the combined effectiveness of provider and community interventions in improving adherence to the T3 initiative among OTCMS in rural Ghana.

**Ethical clearance:**

NMIMR-IRB CPN 086/18-19

**Trial registration:**

ISRCTN registry ISRCTN77836926. Registered on 4 November 2019.

## Background

Malaria has been managed over the years using two approaches: presumptive and test-based [1]. Presumptive treatment of malaria was practiced for decades before the World Health Organization (WHO) approved a shift in policy [2, 3]. Presently, WHO recommends treatment based on clinical grounds only if diagnostic testing is unavailable within 2 h of patients presenting for treatment, and this is necessary to effect cure and prevent life-threatening complications [4].

Prompt and accurate diagnosis of malaria is important for both rapid and effective disease management and surveillance [5]. Malaria diagnosis involves identifying malaria parasites or antigens/products in a patient’s blood [6]. Three diagnostic tools are currently in use to detect malaria parasites in infected humans: light microscopy; nucleic acid amplification (NAA) tests, most often polymerase chain reaction (PCR) based; and rapid diagnostic test (RDT) kits. Each of these tools has advantages and disadvantages. Light microscopy (often called the “gold standard” and the oldest laboratory method) detects malaria parasite species and developmental stages, can be used to quantify parasitemia, and is preferable in investigating malaria treatment failures [5, 7]. PCR detects drug-resistant parasites and may be automated to process large samples, but foremost of its advantage is higher sensitivity and specificity, that is, detects low-density malaria infections [8–10]. With respect to limitations, both light microscopy and PCR are labor intensive, are time consuming, and require trained technicians for reliable results [6]. WHO’s quest for a simple, fast, accurate, and cost-effective diagnostic test for determining the presence of malaria parasites, especially in field situations, led to the invention of malaria rapid diagnostic test (mRDT) kits [11].

mRDT kit is a device that detects specific *Plasmodium* antigen in a small quantity of fresh blood using lateral flow immunochromatography [12]. The main advantages of mRDT kits are that they require no capital investment or electricity, are simple to perform, and are easy to interpret [13]. In sub-Saharan Africa, the deployment of mRDT has increased over the past decade with much focus on the public health sector. Unfortunately, the availability and use of diagnostic testing is low among private medicine retail outlets, including pharmacies and over-the-counter medicine sellers (OTCMS), where many patients with malaria-like symptoms seek treatment [14]. Given the importance of private medicine retail sellers as a first point of care and antimalarial treatment, several endemic countries in sub-Saharan Africa and Southeast Asia are considering introducing and scaling up the use of mRDTs in these outlets to achieve universal access to prompt parasite-based diagnosis before treatment [15].

OTCMS are usually the first point of call for patients in Ghana because there are no consultation fees, little or no waiting times, and patients’ preference for self-medication. OTCMS typically operate in rural areas and are limited by the Pharmacy Act of Ghana to selling only class C (over the counter) medicines which includes antimalarial drugs. As of 2012, there were over 13,000 licensed OTCMS in Ghana out of which 233 had been accredited by the National Health Insurance Authority [16].

Studies on perception of community members and OTCMS in Ghana on proposed implementation and scale up of mRDT in malaria diagnosis reported between 67 and 97% willingness to use mRDT [17, 18]. Ansah et al., in a study conducted in Ghana, reported 100% uptake of RDT, 97% of those testing negative not receiving ACT or antimalarial medicine, and 99% of those testing positive receiving ACT, but data collection was based on provider records only [19]. Similar studies across sub-Saharan Africa using “mystery shopper” and “exit interview” as methods of collecting data recorded widely varied uptake of RDT from 8 to 88% [14]. Despite the encouraging report of mRDT uptake which is above average in Ghana, adherence to mRDT-negative test result is very low. Studies have shown that 62.0% of mRDT-negative clients were given artemether-lumefantrine, and about 30% of OTCMS and some community members held the view that mRDT-negative results did not mean no malaria illness and would therefore use ACT [17, 20].

Provision of artemisinin-based combination therapies (ACTs) and other antimalarials without a confirmed malaria test frequently results in overtreatment of malaria and reduces the availability of ACTs for true malaria cases and potentially delays the diagnosis and treatment of other causes of illness [14]. Hence, this study is aimed at improving implementation of the T3 (test, treat, and track) strategy in the informal healthcare sector [15] using a number of intervention tools that could be scaled-up easily, unlike other studies, at the national level. This will help achieve universal access to prompt parasite-based diagnosis, reduce overprescribing of antimalarial to malaria-negative clients, and promote the tracking of malaria cases.

## Methods/design

### Study design

The proposed interventions will be evaluated using a two-arm (intervention and control), cluster randomized trial across 8 rural clusters (4 clusters per arm), in two adjacent districts of Ghana. The method of Wiseman et al. will be used in this study with some modifications [21]. Wiseman et al. used a three-arm stratified cluster randomized trial to evaluate the effectiveness and cost-effectiveness of two interventions designed to support the roll-out of mRDTs and improve the rational use of ACTs. They focused in part on private medicine retail outlets (known as OTCMS in Ghana), who are the focus of this study. Wiseman et al. looked at the effectiveness of individual interventions, but this study will evaluate the combined effectiveness of different interventions.

A cluster is defined as a geographical community which contains at least one OTCMS, and this will be the unit of randomization within each study arm.

The intervention arm has 8 clusters, and out of these, 4 will be randomly selected using a computer-generated list. The control arm has 4 clusters, and all these will be included in the study (Fig. 1). An urban sub-district (Begoro) in the intervention district will act as a buffer between the two arms. This method is adopted to reduce contamination (that is, filtering of information across the two arms) to the barest minimum. The selected four clusters per study arm will yield a total of 8 OTCMS in the intervention arm and 5 OTCMS in the control arm.

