### Study area

The study will be conducted in the Fanteakwa North and Fanteakwa South districts (previously one district) in the eastern region of Ghana (Fig. 2). The capital of Fanteakwa North district is Begoro (acting as buffer) while the capital of Fanteakwa South district is Osino. The two districts cover an area of 1150 km^2^ with resident population of approximately 108,614 as of 2010. The Fanteakwa North has 5 sub-districts (one urban and four rural) while Fanteakwa South has 2 sub-districts (one urban and one rural). The two districts are characterized by double maxima rainfall in March to October, and November to February respectively, with the highest rainfall in June. They have an annual average temperature of 24 °C. The population is made up of subsistence farmers involved predominantly in crop farming and livestock rearing. The Fanteakwa North district has 1 hospital, no health center, 1 clinic, 31 community health-based planning services (CHPS) compounds, and 28 OTCMS, while the Fanteakwa South has no hospital, 2 health centers, 1 clinic, 15 CHPS compounds, and 19 OTCMS [22].

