## Discussion

The goal of this cluster randomized controlled trial is to evaluate the combined effectiveness of provider and community interventions at improving the implementation of WHO’s T3 malaria initiative in the informal health sector in Ghana.

This trial is unique in 2 approaches. The first relates to the cost of mRDTs. mRDTs will be supplied to OTCMS at no cost to the operators. Also, the retail price for mRDTs will be pegged at the current market wholesale price. It is expected that this approach will ensure that individuals visiting OTCMS with suspected uncomplicated malaria will have a test done at a highly subsidized price while OTCMS benefit significantly. The second approach relates to regular monitoring of the activities of OTCMS. It is expected that the deployment of a surveillance tool and regular/quarterly support visits to the OTCMS will go a long way to improve on adherence to the T3 policy.

In designing this study, the main obstacle to overcome is how to ensure limited or no contamination within the control arm. Two measures are being taken: creating a buffer sub-district between the two arms and investigators engaging OTCMS directly rather than using third parties such as the leadership of the association of OTCMS at the district and regional levels.

If the trial shows that provider and community interventions deployed improved adherence to the T3 policy, the NMCP and related non-governmental organizations will be empowered with this evidence to effectively play their advocacy roles in support of the informal health sector, particularly OTCMS.

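### Communities are randomly sampled within a pre-set intervention arm, not randomly allocated to arms, so the cluster-randomised label is wrong as written and arm is apparently confounded with district

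*Protocol article*

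**What the plan says.** The Protocol article's Study design section describes a two-arm "cluster randomized trial across 8 rural clusters (4 clusters per arm), in two adjacent districts of Ghana". The Abstract uses the same label, and the Discussion repeats it: "The goal of this cluster randomized controlled trial is to evaluate the combined effectiveness of provider and community interventions".

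The mechanics are in the same Study design section. A cluster is a community with at least one medicine seller, and "this will be the unit of randomization within each study arm". For the intervention side: "The intervention arm has 8 clusters, and out of these, 4 will be randomly selected using a computer-generated list". For the control side: "The control arm has 4 clusters, and all these will be included in the study". On geography: "An urban sub-district (Begoro) in the intervention district will act as a buffer between the two arms". The Study area section then says which district that is: "The capital of Fanteakwa North district is Begoro (acting as buffer) while the capital of Fanteakwa South district is Osino".

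Three other sections bear on the point:

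- **Baseline phase and Inclusion criteria:** the baseline household survey is confined to the intervention arm. The end-line survey, which measures the primary outcome, covers both arms.
- **Data management and analysis:** the intervention effect comes from a logistic model with a random effect for within-cluster correlation.
- **Study design and Discussion:** the layout and the buffer are justified by the wish to limit contamination.

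**The concern.** Randomisation in a two-arm trial means that chance decides which units receive the intervention. Here the arms are in place before the computer list is run. The list decides which intervention communities are studied, not which communities are treated. As described, no community could have ended up in the other arm.

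If each arm is also a single district, anything that differs between the districts and affects testing at medicine sellers is carried into the arm difference. The primary objective is that between-arm comparison, and the Discussion intends the result as evidence for the national malaria programme. Under the present label, readers and evidence synthesisers would classify a two-district comparison as a randomised trial, and would read its p-value and confidence interval as protected by randomisation when they are not.

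**Working it through.** **Step 1: is there a random allocation?**

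| Step described | Units | Random? | Decides arm? |
|---|---|---|---|
| Intervention communities | 4 drawn from 8 | Yes | No, the arm is already fixed |
| Control communities | 4 of 4 taken | No | No |
| Choice of intervention district | Not described | Not described | – |

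The phrase "this will be the unit of randomization within each study arm" fits this reading: the random step operates within an arm, not between arms.

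**Step 2: does arm equal district?** The buffer sub-district lies in what the article calls the intervention district and separates the arms. Begoro is the capital of Fanteakwa North, so that is the intervention district. With two adjacent districts in the study, control is by inference Fanteakwa South. No sentence says so, and Fig. 1 is not shown.

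**Step 3: can the planned analysis separate the two?** With one district per arm, a district term is collinear with arm, and between-district variance has zero degrees of freedom. A community random effect captures variation between communities within an arm, not a shift common to all communities in a district. A larger sample does not help. With no control baseline, the change in control cannot be subtracted from the change in intervention.

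**Step 4: how large could the distortion be?** This is an illustration, because the documents give no district variance.

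Inputs from Sample size estimation, Household survey: 412 children in 4 clusters per arm, control rate 10%, intracluster coefficient 0.02, average cluster size 97. The plan's variance inflation factor reproduces: 1 + (97 − 1) × 0.02 = 2.92.

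Assumption: 412 is read as per arm, which the wording leaves open.

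- Cluster size: 412/4 = 103. Design effect: 1 + 102 × 0.02 = 3.04.
- Effective sample size per arm: 412/3.04 = 135.5.
- Null SE of the arm difference: √(2 × 0.10 × 0.90/135.5) = 0.0364, or about 3.6 points.
- Nominal 5% rejection limit: 1.96 × 0.0364 = 0.0714.

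If district rates vary with SD s, the difference between two untreated districts has variance 2s². The true SD of the arm difference is then √(0.0364² + 2s²), and the false-positive rate is 2 × [1 − Φ(0.0714/that SD)].

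| Assumed district SD s | SD of arm difference | Limit/SD | False-positive rate |
|---|---|---|---|
| 0 | 0.0364 | 1.96 | 5% |
| 1 point | 0.0391 | 1.83 | 7% |
| 2 points | 0.0461 | 1.55 | 12% |
| 3 points | 0.0559 | 1.28 | 20% |
| 4.2 points | 0.0702 | 1.02 | 31% |

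The last row is the SD that the plan's own coefficient of 0.02 implies between communities: √(0.02 × 0.10 × 0.90) = 0.0424. It serves as an upper reference: districts varying as much as single communities.

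If 412 is instead the total (206 per arm, 51.5 per cluster), the design effect is 1 + 50.5 × 0.02 = 2.01, the effective size 206/2.01 = 102.5 and the null SE 0.0419. The four non-zero rows become about 6%, 10%, 17% and 26%.

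**The case against.** The layout has a stated reason. Testing advice spreads by word of mouth, so keeping the arms apart with a buffer between them is a defensible way to limit contamination. The two districts were until recently one, and the article describes their climate and population together, which gives some ground for expecting similarity. This explains the choice and makes a very large district gap less likely. It does not turn selection into allocation.

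It is also fair that the one-district-per-arm reading is partly inferred, and that a random choice between the two districts is neither stated nor excluded. Even if a coin had been tossed, there would be one randomised unit per arm and district would remain fully confounded.

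Three stronger readings are tempting but not supported:

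- **That the districts are shown to differ in care seeking.** The Study area section lists facility counts: North has 1 hospital, no health center, 31 CHPS compounds and 28 medicine sellers; South has no hospital, 2 health centers, 15 CHPS compounds and 19 medicine sellers. These are district-wide counts, not rates per head. They include the urban buffer area and say nothing direct about testing or care seeking in the rural clusters.
- **That false positives must be very frequent.** A district SD of 5 points would give about 37%. But it implies a district-level coefficient of 0.05²/0.09 = 0.028, more than the plan assumes between communities, with nothing in the documents to support it.
- **That stamped test kits would reveal leakage if communities were re-allocated.** Stamps trace kits. The contamination that the article is concerned with is the spread of information.

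**Conclusion.** The point stands. The Study design section describes random sampling of intervention communities and complete inclusion of control communities, so the cluster-randomised label in the Abstract, Study design and Discussion states a property that the described design does not have. This part rests on the text alone.

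That district is fully confounded with arm rests on a strong inference about where the control communities lie. Given that inference, neither the planned model nor the intervention-only baseline survey can resolve it.

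The size is unknown. The 7% to 31% range is conditional on assumed district SDs of 1 to 4.2 points, a 10% testing rate, a normal approximation and 412 read as per arm. It shows that modest district differences are enough to undermine a nominal 5% test. It does not show that such differences exist here. The label should be corrected before results are reported.

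**What to change.** **Main change.** In the Abstract, Study design and Discussion, describe a non-randomised controlled cluster study in which arm is set by district and four of the eight intervention communities are randomly sampled. Name the control district. Make any registry entry consistent with this; its content is not visible here. State in the analysis and conclusions that the arm effect is confounded with district and is not randomised evidence. The cost is a few sentences and a more modest conclusion.

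**Possible mitigation.** If the interventions have not yet been deployed, a baseline household survey in the control communities would allow a before-after contrast between districts. That would remove a stable district difference but not one that changes over time, and the comparison would still not be randomised. It costs one additional survey round in four communities.

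**Secondary option, only if still feasible.** Keep eight communities and randomise two of four to each arm within each district. This needs no additional clusters or children, but it has clear downsides:

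- It gives up the geographic separation chosen to limit contamination.
- It allows only C(4,2)² = 36 allocations, so the smallest two-sided permutation p-value is 2/36 = 0.056.
- Recruitment began in September 2019 according to Trial status, so it may be too late.

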**Fig. 1 Fig1:**
[figure not shown]
Flow chart on the study design

The primary objective of the study is to evaluate the combined effectiveness of provider and community interventions by comparing malaria RDT testing rates between the intervention and control arms. The secondary objectives include:
(i)To reduce the proportion of children under 10 years who receive treatment for malaria without testing by over-the-counter medicine sellers (OTCMS) following implementation of different levels of intervention.(ii)To determine the level of service provider (OTCMS) adherence to malaria case management guidelines.

The standard protocol items: Recommendations for intervention trials (SPIRIT 2013) checklist is presented as Additional file 1.

### Study area

The study will be conducted in the Fanteakwa North and Fanteakwa South districts (previously one district) in the eastern region of Ghana (Fig. 2). The capital of Fanteakwa North district is Begoro (acting as buffer) while the capital of Fanteakwa South district is Osino. The two districts cover an area of 1150 km^2^ with resident population of approximately 108,614 as of 2010. The Fanteakwa North has 5 sub-districts (one urban and four rural) while Fanteakwa South has 2 sub-districts (one urban and one rural). The two districts are characterized by double maxima rainfall in March to October, and November to February respectively, with the highest rainfall in June. They have an annual average temperature of 24 °C. The population is made up of subsistence farmers involved predominantly in crop farming and livestock rearing. The Fanteakwa North district has 1 hospital, no health center, 1 clinic, 31 community health-based planning services (CHPS) compounds, and 28 OTCMS, while the Fanteakwa South has no hospital, 2 health centers, 1 clinic, 15 CHPS compounds, and 19 OTCMS [22].

**Fig. 2 Fig2:**
[figure not shown]
Map showing the Fanteakwa North and South districts (formerly one district—Fanteakwa)

### Study procedures

The study has 4 phases. These are preparatory, baseline, intervention, and evaluation (Table 1).

**Table 1 Tab1:**
[figure not shown]
Timelines for study procedures

#### Preparatory phase

The preparatory phase will involve scheduled meetings with stakeholders including the district and regional health directorates, the National Malaria Control Programme (NMCP), relevant non-governmental organizations such as Strengthening Health Outcomes through the Private Sector (SHOPS), and OTCMS and traditional leaders in the selected communities. These engagements will create the required awareness and subsequently obtain permissions and support in the conduct of the study.

As part of the preparatory phase, houses in the selected clusters will be mapped, and lists of households with children under 10 years old will be generated with corresponding GPS coordinates.

